### Intervention

An overview of the study design and analytical workflow is shown in **Figure 1**. Healthy, osteopenic, and osteoporotic (fractured and non-fractured) patients of both sexes, with available DXA or, for fractured patients, DXA prescribed as per clinical practice for secondary prevention, are enrolled during outpatient visits and/or upon admission to the emergency department and/or hospital, after signing written informed consent. Subsequently, a blood sample (2–5 mL) is collected from each enrolled patient and used for PBMC isolation, performed through density gradient centrifugation, and for serum collection. Once isolated, a portion of PBMCs is cultured *in vitro* (without differentiation factors normally required for PBMCs viability maintenance and differentiation) to assess their viability, number, size, and differentiation into osteoclasts. PBMCs viability are evaluated using optical microscopy and the Alamar Blue assay (a non-toxic reagent that assesses cellular activity through the chemical reduction of resazurin to resorufin in the mitochondria of living cells) at 48, 72, and 96 hours and at 1 and 2 weeks. At the same time points, PBMCs number and size (diameter in µm) are also assessed. Finally, at 2 weeks, spontaneous osteoclastogenesis, i.e., the ability of PBMCs to spontaneously become osteoclasts, is evaluated and quantified through immunocytochemical analysis (Tartrate-Resistant Acid Phosphatase - TRAP - staining) and gene expression analysis *via* RT-PCR (Tumor Necrosis Factor alpha - TNF-α, Receptor Activator of Nuclear Factor κB Ligand – RANKL, Macrophage Colony-Stimulating Factor - M-CSF, Parathyroid Hormone - PTH). Differences in PBMCs viability, number, size, differentiation, and/or activity are also be analyzed considering gender differences. To achieve the secondary objectives of the protocol, a PBMCs aliquot undergoes immunophenotypic characterization to identify the T lymphocyte cell phenotype and evaluate its subpopulations. Specifically, the Th1 (CXCR3, CCR5), Th2 (CRTH2, CCR4, CCR3), Th17 (CCR6 and RORC), and TReg (CD25, CD26, CD127low) subpopulations are analyzed by flow cytometry. Biochemical levels of pro- and anti-inflammatory cytokines are assessed in serum samples from enrolled patients (interleukin (IL)-1, IL-2, IL-3, IL-4, IL-5, IL-9, IL-10, IL-17, IL-21, IL-22, IL-33, TNF-α, Interferon gamma - IFN-γ). Moreover, serum samples are also used to evaluate key markers of bone turnover, including bone-specific alkaline phosphatase, procollagen type I N-terminal propeptide (markers of bone formation) and N- and C-terminal telopeptides of collagen I (markers of bone resorption).

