
### Objectives and trial design

#### Primary objective

To analyze the viability, number, size, and differentiation time of PBMCs isolated from peripheral blood samples (2–5 ml) of non-osteopenic and non-osteoporotic patients (hereafter referred to as healthy patients), osteopenic patients, and osteoporotic patients (both fractured and non-fractured) with available DXA or, for fractured patients, DXA prescribed as per clinical practice for secondary prevention.

The aim is to evaluate the sensitivity and specificity of a diagnostic test based on the *in vitro* maintenance and differentiation of PBMCs (European Patent IOR No. 3008470, March 21, 2018) through a multicenter cross-sectional clinical study. Patients are stratified based on their BMD DXA T-score into osteoporotic, fractured and non-fractured (BMD T-score: < -2.5), osteopenic (BMD T-score: -2.5 < T-score < -1), and healthy (BMD T-score: ≥ 1). In accordance with secondary prevention guidelines, patients with a fragility fracture are categorized as ‘osteoporotic fractured’, irrespective of their exact BMD T-score. All assessments are conducted also considering specific gender differences.

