#### Exclusion criteria

Ø Hematopoietic system diseases;Ø Bleeding disorders;Ø Infections (also positive for HIV-HBV-HCV);Ø Neoplastic pathologies;Ø State of pregnancy or breast-feeding;Ø Alcohol use (>20g alcohol per day currently or previously);Ø Smoking (>10 cigarettes per day currently or previously);Ø Diabetes.

Smoking and diabetes conditions were excluded to minimize major confounding effects on immune, metabolic, and inflammatory parameters that could interfere with the interpretation of PBMC behavior independently from bone status.

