### Participant timeline

The study has a total duration of 24 months. Ethical approval was obtained on June 20, 2024. Patient enrolment started on 30 August 2024. The conclusion of the study is foreseen before the end of August 2026. After the enrolment, patients undergo blood sampling.

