### Recruitment

Healthy individuals, osteopenic patients, and osteoporotic patients (both fractured and non-fractured), of both sexes, are recruited for the study. Eligibility is confirmed based on the availability of a recent DXA scan, or in the case of fractured patients, a DXA prescribed as part of standard clinical practice for secondary prevention. Recruitment takes place during outpatient visits, upon admission to the emergency department, or during hospitalization. All participants are enrolled after providing written informed consent.

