## Strengths and limitations of this study

*-Innovative Diagnostic Approach*.

This study investigates a novel, patented PBMC-based method for OP screening and stratification. By relying on simple blood collection and *in vitro* PBMC behavior, this approach offers a potentially accessible, low-cost, and portable alternative to current diagnostic tools such as DXA and FRAX, which show important limitations.

*-Gender-Specific and Multi-Parameter Evaluation*.

A key strength is the integration of gender-specific analysis and the correlation of PBMC behavior with platelet indices, lymphocyte subpopulations, inflammatory cytokines, and bone turnover markers. This comprehensive profiling may lead to a more precise understanding of OP pathophysiology and risk across different patient subgroups.

*-Double-Blind Design and Multicenter Validation*.

The study design includes a partial double-blind approach to reduce laboratory and interpretation bias, and involves two geographically distinct centers in Italy, strengthening the reproducibility and generalizability of results across different populations.

*-Non-Randomized Design*.

A limitation is the non-randomized nature of the study, which does not allow for assessment of causality or longitudinal changes. While stratification is rigorous, observational bias cannot be entirely ruled out.

*-Restricted Population and Potential Confounders*.

Although several confounding factors (e.g., BMI, comorbidities, substance use) are excluded by design, the inclusion of only patients with recent DXA and a limited age range (>40 years) may reduce generalizability to younger populations or those without DXA access.

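### Blood may be drawn during an acute fracture admission, and bone-active drugs are not addressed, so the fractured group's markers may partly reflect injury or treatment

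*Protocol article*

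**What the plan says.** **Where and when patients are sampled.** The Intervention section says that participants of all four groups "are enrolled during outpatient visits and/or upon admission to the emergency department and/or hospital, after signing written informed consent". The Recruitment section repeats it: "Recruitment takes place during outpatient visits, upon admission to the emergency department, or during hospitalization". The Participant timeline section fixes only the order: "After the enrolment, patients undergo blood sampling". No section states an interval between fracture or surgery and the blood draw, or requires the same setting across groups.

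**Who is in the fractured group.** Under Primary objective, "patients with a fragility fracture are categorized as ‘osteoporotic fractured’, irrespective of their exact BMD T-score". This is also the only group that may enter with a scan still to be done: "for fractured patients, DXA prescribed as per clinical practice for secondary prevention" (Intervention).

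**What is excluded, and why.** The Exclusion criteria cover blood and bleeding disorders, infection, neoplasia, pregnancy or breast-feeding, alcohol, smoking and diabetes. The reason given is general: "Smoking and diabetes conditions were excluded to minimize major confounding effects on immune, metabolic, and inflammatory parameters". The stated worry is that such effects would cloud the reading of the PBMC results for reasons other than bone. Recent trauma or surgery, osteoporosis drugs and systemic glucocorticoids are not mentioned.

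**What the analysis conditions on.** The Statistical methods section uses T-score and gender as strata. It lists general linear models but names no covariate for setting, time since fracture or treatment. The limitations section says "Although several confounding factors (e.g., BMI, comorbidities, substance use) are excluded by design" and does not name acute injury or treatment.

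**The concern.** The measures under study are PBMC viability, number, size and spontaneous osteoclast formation, T-cell subsets, cytokines, platelet indices and bone-turnover markers. All are immune, inflammatory, haematological or bone-turnover measures. The authors remove smokers and diabetics because such measures can move for reasons unrelated to bone status. The same reasoning applies to a recent fracture, an operation, an osteoporosis drug or a systemic glucocorticoid, and each of these is plausibly more common in one or both osteoporotic groups than in the healthy group.

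Two things are at stake. The primary aim is the sensitivity and specificity of the PBMC test, and 30 of the 60 osteoporotic participants are fractured. The article also wants to relate PBMC behaviour to severity, from osteopenia to fragility fracture. The last step of that gradient, non-fractured to fractured, cannot separate severity from recent injury if fractured patients are mostly sampled acutely. If timing and drug use are not recorded, no later analysis can repair this.

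**Working it through.** **Inputs from the protocol article.** Four groups of 30, 120 in total (Allocation, Statistical methods). Chi-square test on viability yes/no, w = 0.33, alpha 0.05, power 0.80, 20% drop-out (Statistical methods). The article gives no size or sign for the effect of injury or drugs on any marker, so the shifts below are assumptions.

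**Step 1. The plan's own figure.** A four-group by yes/no table has df = (4 − 1)(2 − 1) = 3. With w = 0.33, the noncentral chi-square reaches 0.80 power at N = 101, and power at N = 100 is 0.799. Adding 20% gives 100 × 1.2 = 120, the stated total. The powered test is therefore a comparison of all four groups, and the fractured group is one of the four.

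**Step 2. Effect on the powered test.** Assume no osteoporosis effect: three groups have viability rate p0, and the fractured group alone has p0 + d because of injury or treatment. Then w² = [Σ(p_i − p̄)²/4] / [p̄(1 − p̄)].

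Example with p0 = 0.30 and d = 0.20: p̄ = 0.35, Σ(p_i − p̄)² = 3 × 0.0025 + 0.0225 = 0.03, w² = 0.0075/0.2275 = 0.033, w = 0.18.

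| d | P(reject), N = 120 | P(reject), N = 96 (20% lost) |
|---|---|---|
| 0.10 | 0.11–0.12 | 0.10 |
| 0.20 | 0.33–0.36 | 0.27–0.29 |
| 0.30 | 0.67–0.69 | 0.56–0.58 |
| 0.40 | 0.92 | 0.84 |

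The ranges cover p0 = 0.30 and 0.50. The nominal rate is 0.05.

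**Step 3. Effect on AUC.** Assume a normal marker with no osteoporosis effect, shifted by δ SD in patients sampled acutely. One shifted against one unshifted patient gives AUC = Φ(δ/√2). If a fraction f of the comparison's cases is shifted, AUC = 0.5 + f[Φ(δ/√2) − 0.5].

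| Comparison | f | δ = 0.5 | δ = 1.0 | δ = 1.5 |
|---|---|---|---|---|
| Fractured v non-fractured, all 30 acute | 1 | 0.64 | 0.76 | 0.86 |
| Fractured v non-fractured, half acute | 0.5 | 0.57 | 0.63 | 0.68 |
| Both osteoporotic groups v the rest (60 v 60), all 30 acute | 0.5 | 0.57 | 0.63 | 0.68 |
| Same pooled comparison, half acute | 0.25 | 0.53 | 0.57 | 0.59 |

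All these values would be 0.50 without the shift. A shift in the opposite direction gives the mirror image below 0.50. If there is a real disease effect, a shift against it would lower the apparent accuracy.

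**Step 4. Precision if accuracy is reported by group.** The 95% half-width at 80% sensitivity is 1.96 × √(0.16/n): 0.143 at n = 30, 0.160 at n = 24 (30 less 20%), and 0.101 at n = 60.

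**The case against.** Several points on the other side are fair.

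- **Setting by group.** A reader might infer that fractured patients come from emergency care and everyone else from outpatient visits. The article does not say so. It lists the settings once for all groups, and a fractured patient may be enrolled as an outpatient with a scan already available. The inference is reasonable, because the group is defined by the fracture and only this group has the prescribed-scan route, but the fraction sampled acutely is unknown.
- **Direction.** A reader might conclude that sensitivity and AUC are inflated. Nothing in the article gives the sign of an injury or drug effect on PBMC behaviour, and drug effects could go either way. Only confounding of unknown direction is supported.
- **Pooling.** A reader might take the 60 v 60 comparison as the planned analysis. Allocation treats the osteoporotic patients as one main group with two subgroups, which suggests it, but the powered test keeps four groups. The pooled figures are conditional on pooling.
- **Unseen material.** The CRF fields are not shown. Dates and drugs may already be recorded, and covariates or sensitivity analyses may be in the full protocol or SAP. The limitations section also concedes some observational bias.

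These points limit how strongly the concern can be put, but they do not remove it. The eligibility lists, their rationale and the enrolment settings are printed in the article. As written they permit acute sampling and leave these drugs unaddressed.

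**Conclusion.** The concern holds as a risk of confounding. The design as printed allows the fractured group's markers to be mixed with the effects of acute injury, and those of either osteoporotic group with the effects of treatment. The exclusions do not cover these sources, although their own rationale would.

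Its size depends on two unknowns: the fraction of fractured patients bled acutely and the shift that injury or treatment causes. Under the assumed shifts of 0.5 to 1.5 SD and no disease effect, the fractured versus non-fractured comparison is the most exposed, and the pooled comparison moves about half as far from 0.50. These figures illustrate what could happen and do not predict this trial's result.

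The article does not support saying that accuracy is certainly inflated, that the other groups are outpatients, or that a pooled headline is planned. Nor does the concern require dropping fractured patients from the headline, which would be a debatable choice for a test meant to stratify fracture risk. What it supports is a cheap improvement in recording and reporting.

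**What to change.** 1. Make sure the CRF captures enrolment setting, fracture date, blood-draw date, whether surgery preceded the draw, and current osteoporosis drugs and systemic glucocorticoids. For patients already enrolled, retrieve these from the charts.
2. Report sensitivity and AUC separately for non-fractured and fractured osteoporotic patients, alongside any pooled figure.
3. Prespecify sensitivity analyses that exclude, or adjust for, patients bled during the acute admission and patients on the recorded drugs.
4. Name acute injury and treatment as possible confounders in the limitations section.

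Any clinical cut-off for timing or treatment is for the investigators to set.

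**Cost.** A few chart-based fields and some analysis wording. Group-specific sensitivity is less precise: about ±14 points on 30 patients, or ±16 on 24, against about ±10 on 60. Enrolment began in August 2024 and the study is due to end before the end of August 2026, so recording is best settled now.

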
**Figure 1 f1:**
[figure not shown]
Schematic representation of the study protocol: 120 patients with DXA available or clinically indicated are enrolled. Standard blood analysis is performed alongside a 2–5 mL blood draw used for PBMC isolation and serum collection. PBMCs are divided for immunophenotyping and *in vitro* culture to assess viability, size, spontaneous osteoclastogenesis, and gene expression. Serum cytokines, platelet-related markers, and bone turnover markers are analyzed. Correlation of all variables allows patient stratification.

Given the key role of platelets (PLT) and platelet-related parameters in OP, T lymphocyte activation, and pro-inflammatory cytokine production (11), specific laboratory parameters related to platelets, such as PLTs count, Platelet Distribution Width (PDW), Mean Platelet Volume (MPV), Platelet Hematocrit (PCT), Platelet-to-Lymphocyte Ratio (PLR), and Red cell Distribution Width-to-Platelet Ratio (RPR), are also collected and analyzed. All parameters are analyzed considering gender differences.

Finally, to assess the relationship among all analyzed variables—BMD through DXA T-score, PBMCs viability, number, size, and differentiation, T lymphocyte subpopulations, pro- and anti-inflammatory factors, biochemical markers of bone turnover and PLT and platelet-related parameters in blood and serum samples from healthy individuals and osteopenic and osteoporotic (fractured and non-fractured) patients—a correlation study are conducted.

### Expected outcomes

This trial will enable the investigation of PBMCs’ *in vitro* behavior in relation to varying degrees of altered bone metabolism, ranging from osteopenia to fragility fractures. It will also assess correlations with specific blood and serum factors involved in the pathogenesis of osteoporosis, such as T-lymphocytes, platelet parameters, and pro-inflammatory cytokines.

These findings may contribute to enhancing the functionality of the Rizzoli European patent (No. 3008470), including in a gender-specific context, and support the development of the prototype tool already described in the filed patent.

The knowledge gained from this study will provide the National and International Health Care Systems with a safe, functional, high-quality, user-friendly, low-cost, and low-power consumption device, suitable for widespread routine use — particularly in low-income countries.

### Participant timeline

The study has a total duration of 24 months. Ethical approval was obtained on June 20, 2024. Patient enrolment started on 30 August 2024. The conclusion of the study is foreseen before the end of August 2026. After the enrolment, patients undergo blood sampling.

### Recruitment

Healthy individuals, osteopenic patients, and osteoporotic patients (both fractured and non-fractured), of both sexes, are recruited for the study. Eligibility is confirmed based on the availability of a recent DXA scan, or in the case of fractured patients, a DXA prescribed as part of standard clinical practice for secondary prevention. Recruitment takes place during outpatient visits, upon admission to the emergency department, or during hospitalization. All participants are enrolled after providing written informed consent.

### Blinding

This is a double-blind multicenter cross-sectional clinical trial. The application of double-blinding, traditionally associated with interventional studies in which neither participants nor clinicians are aware of key information, typically regarding the assigned treatment, has been adapted in the context of this study to ensure that both laboratory technicians and data analysts remain blinded to the clinical condition of participants. Specifically, the double-blind approach is justified by the following:

- Blinding of laboratory technicians: The laboratory personnel analyzing the biological samples will not have access to information regarding participants’ clinical status. This approach ensures that the laboratory results are obtained objectively, with any observed differences attributable solely to biological variation between groups rather than procedural bias.- Blinding of data evaluators: The researchers responsible for interpreting the final data will be blinded to the clinical conditions of the participants during the analysis phase. This minimizes the risk of interpretative bias and ensures that conclusions are drawn based solely on objective data.

This blinding strategy, which can be described as a partial double-blind, guarantees that all data are processed with consistency and scientific rigor. It enhances the quality and validity of the findings and aligns with best practices for minimizing subjective influence in biomedical research.

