### Statistical methods

Statistical analyses are performed using R software (12) and relevant packages, such as ggplot2 (13), for graphical data visualization. A p-value < 0.05 is considered statistically significant.

A total sample size of 120 patients (n = 30 per group) was calculated using G*Power software (power = 0.80, alpha error probability = 0.05). The estimation was based on a Chi-square test (contingency table) with a medium effect size (w = 0.33), derived from the hypothesized difference in PBMC viability (yes/no) between healthy, osteopenic, and osteoporotic patients (fractured and non-fractured). A 20% potential drop-out rate was also considered in the calculation. This sample size ensures adequate statistical power for the primary outcome while maintaining feasibility across the two recruiting centers.

All data are recorded in an electronic dataset comprising continuous variables (e.g., age, PBMC viability, cell count and size, T lymphocyte subpopulation percentages, expression of pro- and anti-inflammatory cytokines, platelet-related parameters, and bone turnover markers, including BMD T-score), nominal categorical variables (e.g., gender, diagnosis), and ordinal categorical variables (e.g., patient stratification). Univariate analyses are conducted to assess the distribution, central tendency (e.g., mean, median), and dispersion (e.g., standard deviation, variance, interquartile range) of quantitative variables, and the frequency distribution of qualitative variables. Continuous variables showing skewed distributions are transformed to approximate normality.

After assessing normality and homogeneity of variances, appropriate statistical tests are applied. For normally distributed data with equal variances, parametric tests such as ANOVA, General Linear Models (GLM), and Student’s t-test are used. In cases of non-normality or heteroscedasticity, equivalent non-parametric tests (e.g., Kruskal–Wallis and Mann–Whitney U tests) are employed.

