Patients are stratified by BMD T-score and gender. Correlation, regression, and accuracy analyses are performed accordingly. Specifically, the relationship between BMD and PBMCs viability, count, size, differentiation, T lymphocyte subpopulations, inflammatory cytokines, platelet-related parameters, and serum biochemical markers of bone turnover is investigated. Pearson’s correlation coefficient is used for normally distributed data, and Spearman’s rank correlation is applied for non-parametric data. Receiver Operating Characteristic (ROC) curve analysis is conducted to assess the discriminative power of individual variables.

To avoid information loss and potential selection bias, missing values are imputed. When missingness is minimal, single imputation is used; otherwise, multiple imputations are performed, assuming data are missing at random (MAR) (14). Multiple imputation is conducted using the Multivariate Imputation by Chained Equations (MICE) package in R (15).

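### The analyst and interpreter blind cannot be kept for the T-score-based and accuracy analyses, because these use the T-score and diagnosis; the laboratory blind stands

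*Protocol article*

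**What the plan says.** The Blinding section of the protocol article adapts the term double-blind to a cross-sectional study. The stated purpose is "to ensure that both laboratory technicians and data analysts remain blinded to the clinical condition of participants". Two parts follow.

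- Laboratory: "The laboratory personnel analyzing the biological samples will not have access to information regarding participants’ clinical status".
- Evaluation: "The researchers responsible for interpreting the final data will be blinded to the clinical conditions of the participants during the analysis phase".

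The section then qualifies the label: "This blinding strategy, which can be described as a partial double-blind". The Strengths and limitations section repeats the word partial in its text, but its item title is unqualified. So is the description of the study in the Abstract (Methods and analysis).

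The Statistical methods section describes the dataset. Its continuous variables include "platelet-related parameters, and bone turnover markers, including BMD T-score", and it also holds "nominal categorical variables (e.g., gender, diagnosis), and ordinal categorical variables (e.g., patient stratification". On the analyses it says: "Patients are stratified by BMD T-score and gender. Correlation, regression, and accuracy analyses are performed accordingly". It goes on to relate BMD to PBMC viability, count, size and differentiation, to T lymphocyte subpopulations, cytokines, platelet parameters and bone turnover markers, and to run ROC curves on individual variables.

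**The concern.** The two sections cannot both hold for the same people at the same stage. An analyst who correlates T-score with viability, or stratifies by T-score, has the clinical condition on the screen. An interpreter who reads a sensitivity must know which participants count as diseased.

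This matters because the primary objective is the sensitivity and specificity of a new test, and several features of that test leave room for choice. According to the Intervention section, viability is read by optical microscopy and by Alamar Blue at five time points (48, 72 and 96 hours, 1 and 2 weeks). The sample-size paragraph treats viability as yes/no, while the dataset description treats it as continuous, so a dichotomy has to be made somewhere. If the yes/no rule, the read time or the handling of failed cultures is settled after group status is visible, the choice can drift towards whatever separates the groups, and apparent accuracy rises. The evaluator blind is presented as the protection against this kind of interpretive bias. A reader would credit it with a protection that the stated analyses do not allow.

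**Working it through.** No figure in the plan depends on this point, and the sample-size calculation does not involve blinding. The check sets the sections side by side.

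**Step 1. Who is blind, to what, and when.** Blinding covers laboratory technicians, data analysts and those interpreting the final data. The object is the participant's clinical condition. For interpreters the period is the analysis phase.

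**Step 2. What the T-score reveals.** The Allocation section defines the healthy, osteopenic and osteoporotic groups by T-score bands, so anyone who sees a participant's T-score knows the BMD band. It does not reveal fracture status: under the primary objective, a patient with a fragility fracture is classed as osteoporotic fractured whatever the T-score. The dataset closes that gap, because it also holds "nominal categorical variables (e.g., gender, diagnosis".

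**Step 3. Which stated analyses need clinical condition.**

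| Analysis in Statistical methods | Needs T-score or diagnosis in view? | Can the evaluator blind hold? |
|---|---|---|
| Univariate summaries, distribution checks, transformations | No | Yes |
| Comparisons by gender alone | No | Yes |
| Correlations among variables other than BMD | No | Yes |
| Group comparisons (ANOVA, Kruskal–Wallis, chi-square) | Group membership only | Yes, if run on neutral codes |
| Stratification by T-score | Yes | No |
| Correlation and regression of BMD with each marker family | Yes, T-score is the variable | No |
| ROC and accuracy analyses | Yes, reference status is needed | No |

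**Step 4. Whether masking could rescue the last three rows.** Neutral labels (A, B, C, D) hide the meaning of a group, but they cannot hide a T-score that is itself an analysis variable. The unique study code described under Confidentiality and access to data hides identity and leaves clinical condition visible. Sensitivity and specificity cannot be told apart until someone knows which label is the diseased group.

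**Step 5. Whether an unseen document could resolve it.** A full protocol or analysis plan could add masked codes or a data lock. It could not make a T-score analysis blind to the T-score. The conflict therefore lies in what the article states, and does not arise from detail left elsewhere.

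**The case against.** The strongest reply is that the blind that matters most for a microscopy-read test is the laboratory one. It is stated plainly and nothing in the analysis text contradicts it. The authors also say that the term has been adapted, and they call the result partial. This stands. A reader might infer that the study has no blinding worth the name; the documents do not support that. But the qualification does not withdraw the evaluator sentence.

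A reader might also infer that every stated analysis is affected. That is too broad: the first four rows of the table above can be run blind.

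It can be argued that interpreters who see only aggregate output remain blind to individuals. That may be so for interpreters, but the Blinding section also names data analysts, who need individual T-scores to run the models.

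No section provides for re-reading cultures or re-calling viability after unblinding, and laboratory staff are barred from clinical status. This stands too. The route to bias is an opening that the plan leaves, not a practice that it describes. It is tempting to turn hypothetical re-calls into percentage points of sensitivity, but the documents support neither a number of re-calls nor a single denominator. With 30 per group, the diseased group could be 30, 60 or 90, depending on the target condition.

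The Blinding and Strengths sections claim only to minimise or reduce bias, and neither ties the claim to sensitivity or specificity.

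Finally, choosing a cut-off from a ROC curve always uses reference status, whoever is blinded. An analyst blind would not protect that choice, so the cut-off problem is not a consequence of the blinding conflict. The absence of a lock step from a journal article is likewise not a fault in itself. A lock is proposed here because it does the job that the evaluator blind was meant to do.

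**Conclusion.** The concern holds in a limited form. The second of the two blinds cannot operate as written for stratification by T-score, for correlation and regression involving BMD, or for the ROC and accuracy analyses. The laboratory blind stands, and the descriptive and coded-group analyses could be masked.

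The size is the set of analyses affected. It contains the accuracy analysis that serves the primary objective and the BMD correlations that serve a secondary one. No amount of bias can be computed from the documents, and none is claimed.

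The conclusion assumes that the dataset described in Statistical methods is the one the analysts use, and that clinical condition in the Blinding section includes BMD status. Both are the natural reading. The statement should be corrected, but it does not invalidate the design.

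**What to change.** 1. In the Abstract, Blinding and Strengths and limitations sections, describe the study as assessor-blinded. Limit the claim to the readers of the PBMC, cytometry and serum assays. Withdraw the statement that analysts and interpreters are blind during analysis, or confine it to the descriptive and coded-group comparisons if masked codes will really be used.
2. State that assay results, the viable yes/no call, failed-culture exclusions and the primary read time are finalised and locked under the study code. T-score, diagnosis and fracture status are merged only after that, and the merge date is recorded.
3. State that any cut-off chosen from a ROC curve after the merge will be reported as data-derived, since blinding does not protect it.

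The cost is a change of wording and one data-lock step, with no new patients. The downsides are the loss of the unqualified double-blind label and no revision of assay calls after the merge. Timing matters: the Participant timeline has enrolment starting on 30 August 2024 and the study ending before the end of August 2026, and the lock helps only if it is set before the data are linked.
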